## ii. Rationale for Selection of Subject:

**Why youth between 13 and 18 years old?** This investigation is limited to adolescents in this age range because our prior experience working with youth and cognitive interventions indicates that children aged 12 and younger may not be able to cognitively grasp the abstract concepts of cognitive-behavioral therapy. Moreover, depression risk has been shown to increase between ages 14 and 18. Therefore, it makes the most sense to target the intervention to adolescents in this risk period.

**Is an Attention Monitoring Psychoeducation comparison ethical and will it provide adequate attention control?** There is currently no standard of care for adolescents who have depressive symptoms but who do not meet criteria for Major Depressive Disorder (MDD). We believe that this study design is ethical because even adolescents in the HEALTH EDUCATION group will receive a higher standard of care than is traditionally available, including (1) screening, (2) psycho-education, (2) monitoring at 1 week and 1, 2, 6, 12, 18 and 24 months for progression to major depression, (3) feedback when progression occurs, (4) referral to the physician and family in completing treatment referrals, and (5) training of the primary care physician to recognize, treat and/or refer adolescents with major depression, consistent with primary care based Chronic Care Model interventions. By providing the HEALTH EDUCATION adolescents with a psycho-education Internet site, tracking assessment calls and physician encounters, we can actually measure "attention" so as to control for or evaluate effects in the mediation analysis. To address physician contact attention, all HEALTH EDUCATION physician contact will be documented. Furthermore, we estimate that the total study contact experienced by both groups when all assessment, PCP and Internet exposure are included to be 6.5 hours in CATCH-IT 3 and 5.0 hours in HEALTH EDUCATION.

**Why exclude youth with no symptoms of depression, or with current depressive diagnoses?** The goal of the present study is to reduce the risk of depressive episodes among adolescents who are at risk for disorder based on sub-syndromal depressed mood ("Indicated prevention" based on IOM categorization of preventive interventions, presence of symptoms but not reaching criteria for disorder/episode). With regard to enrolling youth with no symptoms, past attempts to prevent depression using a "universal" prevention approach (e.g., targeting all adolescents in a particular school district) have not demonstrated benefit on the whole. In terms of enrolling youth with current disorder, past research suggests that youth with current major depression are less likely to respond to prevention efforts than are "demoralized" youth (i.e., youth with elevated symptoms of depression but no current depressive disorder). Sub-syndromal depressed mood represents a unique opportunity to intervene whereby adolescents are sufficiently "demoralized" to be motivated to participate, but not so depressed that the behavioral intervention may not be effective.

**Why include youth with other psychiatric diagnoses?** The goal of the present study is to examine the efficacy of a *public health* model for the prevention of youth depression in primary care. Given our desire to implement this intervention in real-life settings, and given the high rates of comorbidity in youth with depressive disorders, it follows that a more inclusive recruitment approach is required.

**Why over sample ethnic minority youth?** Most interventions have been developed for European American adolescents. Sources of resiliency and vulnerability may vary by ethnicity in significant ways (see preliminary results). We need a large enough cohort of ethnic minority youth to ensure we can adequately explore these issues.

**Why a stream-lined assessment battery?** The goal of this study is to examine the efficacy of an intervention with very limited person-to-person contact in realistic community settings with a population of primary care patients comparable to the general population of adolescents. We believe, based on our prior survey research, that extensive person-to-person psychological evaluation may alienate many potential study participants. We are thus only conducting a single face-to-face assessment meeting at baseline, and will conduct subsequent assessments via the telephone.

**Why assess parents for depressive symptoms?** Although the focus of the CATCH-IT 3 intervention is on preventing youth depression, for several reasons we are also assessing parental depressive symptoms. First, parental depression is a significant predictor of depression in adolescence. Second, in a multi-site depression prevention study targeting at-risk adolescents, current parental depression was found to modify intervention effects, such that the intervention only decreased the incidence of depression in youth whose parents were not currently depressed. Finally, studies of family-based prevention programs indicate that, in addition to decreasing risk for depression in the youth targeted by the intervention program, these prevention efforts also have decreased depressive symptom levels in parents. We will assess depressive symptoms in parents at each time point and offer parents Internet based resources if they are experiencing depressed mood. We will also examine the moderating and mediating influence of parental mood on outcome.

**Why a two-year follow-up?** Effects from other prevention programs for youth depression have diminished over 22 months. Also, effects from some prevention programs for youth depression have *increased* over time. We will follow participants for 2 years after intake to detect both initial and more enduring aspects of the intervention. Extended follow-up is especially important in *prevention* outcome interventions, because by definition the participants enter this investigation when they are not in an episode of depression and must be followed prospectively to determine if the experimental intervention minimizes or eliminates future episodes.

**Bo**

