Step 7: Primary care physicians will be told to use usual care procedures (e.g., referrals for therapy, medication) in responding to adolescents with major depression during screening or during study participation. In addition, we will provide physicians with written materials and training so that they feel better equipped to manage adolescents who present with depressive issues.

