## e. Description of Procedures

**Random assignment to experimental conditions:** Participants will be assigned randomly to CATCH-IT 3 or HEALTH EDUCATION. Randomization will be blocked by practice and stratified by level of risk, and will be balanced across time. Blocked randomizations will be prepared by the Northwestern site (data analysis site).

Intervention

- I. CATCH-IT 3 intervention defined.** Based on promising results from the phase 2 trial of CATCH-IT 3, a modified version of this primary care/Internet-based preventive intervention is being prepared (text revised and edited, Internet design completed,) titled CATCH-IT 3 revised (CATCH-IT 3), using previously published methods. The CATCH-IT 3 intervention has a motivational (3 PCP motivational interviews at time 0, 2 months and 12 months and 2 check-in phone call at week 1 and week 4 ) and an Internet component (with separate adolescent [14 modules] and parent [5 modules] programs). Parents have a parallel structure of motivational (3 motivational interviews at time 0, 2 months and 12 months, performed by study coordinator) and 2 phone calls at weeks 1 and 4 after enrollment) This revised and expanded intervention will include a comprehensive approach to reducing modifiable risk factors and enhancing resiliency factors associated with increased or decreased risk of depression, respectively, proposed by Spence and [name]. Study staff will monitor time in study and deploy elements of the intervention based on time since enrollment, including computer and human elements (e.g. calls, doctor visits). If study staff are unable to reach participants by phone on the first attempt for any of the above mentioned study procedures, staff will attempt to call two (2) more times over a 1-2 week period to establish contact. If no response is received, staff will try contacting participants by a secondary method as specified in the General Information Sheet (email, mail, or text message). Staff will then wait 2 weeks before contacting the participant again. This process will be repeated until contact with the participant is made or the participant requests to be withdrawn from the study. If withdrawal is requested, a letter confirming their withdrawal will be sent. Details regarding contact of participants and withdrawal procedures can be found in the **Protocol for Contacting Participants and Withdrawal Procedures**.

[figure not shown]

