**J. Attention Monitoring and Psychoeducation Group (“Healthy Lifestyles”) defined:** The HEALTH EDUCATION components (labeled as “Health Education” to participants) are similar to those employed in previous primary care based quality improvement/Chronic Care Model Interventions (patient education [psycho-education described below], provider training [described in Case Finding and Recruitment], active monitoring and referral [case management, discussed under assessments], physician and nurse education and routine contact with PCP [study design rationale]) (see Table 4 below). This Internet site will focus on assisting parents and adolescents with general information on health living appropriate for age as well as psychoeducation about depression. The psychoeducation is intended to assist participants in determining what depressive illness is and what treatment option exist and increase likelihood of seeking treatment. The HEALTH EDUCATION group will receive the same assessments as the CATCH-IT 3 group (including notification and referral) and routine contact with PCP (anticipated 2-3 visits). Psychoeducation Internet site use will be monitored to compare with use of the CATCH-IT 3 intervention as an attention control. Self-harm risk will be managed based on a standard protocol. If study staff are unable to reach participants by phone on the first attempt for any of the above mentioned study procedures, staff will attempt to call two (2) more times over a 1-2 week period to establish contact. If no response is received, staff will try contacting participants by a secondary method as specified in the General Information Sheet (email, mail, or text message). Staff will then wait 2 weeks before contacting the participant again. This process will be repeated until contact with the participant is made or the participant requests to be withdrawn from the study. If withdrawal is requested, a letter confirming their withdrawal will be sent. Details regarding contact of participants and withdrawal procedures can be found in the **Protocol for Contacting Participants** and **Withdrawal Procedures**.

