*Protection for risks associated with potential loss of confidentiality.* Data for all participants will be kept strictly confidential, except as mandated by law. All research files are kept in locked file cabinets or a locked file room. Participants will be assigned a numerical code for identification in the files. Names and other identifiers will be kept in separate locked files. Statistical analyses will be performed on aggregate-level data; participants are never individually named. All audio-recorded assessments and motivational interviews will be kept in locked file cabinets and will never be played for anyone who is not a member of the research team.

D) *Risks of worsening mental or emotional state and or self-harm thoughts/events.* Some youth enrolled in the Internet-based prevention program, and in the control group, will likely develop depression, suicidal behavior, and/or other mental and emotional problems during the study period. The development of suicidal ideation during the study remains as the most serious risk. However, these are risks inherent in the population and would occur whether or not they were enrolled in the study. We do not believe that the risk of these depressive, suicidal, or other adverse outcomes are increased as a function of being enrolled in this study. Should mood worsen or thoughts of self-harm develop (i.e. teen develop MDD, MDE, or suicidal thoughts), the teen's physician and parents will be notified. Physicians will be recontacted 1 week after disclosure to inquire as to whether the teen has begun treatment or a treatment plan is in place. Should no plan/treatment yet be established, PI or Project Manager will discuss with doctor the best course of action for the teen to ensure their safety and connection to mental health services.

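### Contact recorded during follow-up is to be used to control for attention, but physician contact can depend on both arm and outcome, so a contact-adjusted intervention effect is biased in a direction the plan leaves open

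*Protocol*

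**What the plan says.** In the Rationale for Selection of Subject, the protocol asks whether the comparator gives adequate attention control. It answers that by giving the control arm an Internet site and "tracking assessment calls and physician encounters, we can actually measure" attention, the trial can use the measurement "so as to control for or evaluate effects in the mediation analysis". The same paragraph estimates total contact at "6.5 hours in CATCH-IT 3 and 5.0 hours in HEALTH EDUCATION". No counting window is given.

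On how contact relates to **arm**:
- CATCH-IT has "3 PCP motivational interviews at time 0, 2 months and 12 months" (4.e Description of Procedures).
- HEALTH EDUCATION has "routine contact with PCP (anticipated 2-3 visits" (4.e, item J).
- Practices are reimbursed for time at $400 per CATCH-IT participant and $200 per HEALTH EDUCATION participant (item N, Incentives).

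On how contact relates to **outcome**:
- Physicians are to follow usual care "in responding to adolescents with major depression during screening or during study participation" (recruitment of adolescents, Step 7).
- The list of what HEALTH EDUCATION youths receive includes "3) feedback when progression occurs, (4) referral to the physician and family in completing treatment referrals" (Rationale).
- If mood worsens, the physician and parents are notified, and "Physicians will be recontacted 1 week after disclosure to inquire as to whether the teen has begun treatment" (section on risks, item D).

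The Survival analyses paragraph plans a Cox comparison by arm and does not name contact as a covariate. The Mediator analysis paragraph does not list physician encounters or assessment calls.

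**The concern.** A variable that is affected by the arm and also by the outcome is a collider. Conditioning on it links arm and outcome even when the intervention does nothing, and randomisation gives no protection.

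Take counts over the whole follow-up, one extra CATCH-IT visit and one visit triggered per episode. A CATCH-IT youth without an episode then has on average 2.5 + 1 = 3.5 visits, and so does a control youth with an episode. At equal contact, controls are therefore enriched for episodes and CATCH-IT looks protective.

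The choice to evaluate rather than control for attention does not avoid this. With the same variable as a mediator, part of the path from contact to depression would really run from episode to visit. What is at stake is the supplementary argument that any benefit comes from the program and not from the attention around it.

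**Working it through.** **1. Check that the simulation rests on the plan's own event model.** Inputs from Sample Size and Statistical Power: 200 per arm; 72% of controls event-free at one year with the same exponential rate in year two; hazard ratio 0.62; attrition of 7% per quarter in year one and 2% per quarter in year two. Two-sided alpha of 0.05 is assumed for Aim 1.

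- Control hazard = −ln(0.72) = 0.3285 per year.
- With continuous attrition, the event probabilities over 24 months are 0.390 and 0.269. Expected events = 200 × (0.3901 + 0.2689) = 131.8.
- Power = Φ(√E × |ln HR| / 2 − 1.96) = Φ(11.48 × 0.478 / 2 − 1.96) = Φ(0.784) = 78.4%.
- With attrition at the end of each quarter, E = 135.3 and power = Φ(11.63 × 0.478 / 2 − 1.96) = Φ(0.820) = 79.4%.

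The stated 80% is reproduced to within two points, so the same hazard and attrition are used below.

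**2. Null simulation, counts over the whole follow-up.** True hazard ratio 1, 200 per arm, 600 trials per setting, Cox model with arm and visit count. The documents give no figures for the visit process, so these are assumptions:
- background visits are Poisson with mean 2.5 in both arms (the middle of the anticipated 2-3), whether or not a youth drops out;
- extra CATCH-IT visits range from 0 to 1, which is the gap when 3 interviews are set against 2-3 visits;
- triggered visits per episode range from 0 to 2.

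| Extra CATCH-IT visits | Triggered visits per episode | Adjusted HR | False benefit |
|---|---|---|---|
| 0 | 0 to 2 | 0.99 to 1.01 | 1.7% to 3.2% |
| 0.5 | 0 | 0.99 | 1.7% |
| 0.5 | 0.5 | 0.94 | 4.0% |
| 0.5 | 1 | 0.90 | 7.7% |
| 0.5 | 2 | 0.85 | 17.2% |
| 1 | 0 | 1.00 | 2.2% |
| 1 | 0.5 | 0.88 | 11.0% |
| 1 | 1 | 0.81 | 26.7% |
| 1 | 2 | 0.73 | 47.5% |

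The nominal rate of false benefit is 2.5%. The cell with 0.5 and 0.5, repeated with 3,000 trials, gave 0.94 and 5.7%, so about 6% is the better figure there. The unadjusted hazard ratio in these settings was 0.99 to 1.01, with total rejection about 5%.

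**3. Other counting rules, true hazard ratio still 1.**
- Visits summed only up to the episode or dropout and entered as a fixed covariate: adjusted HR 1.9 with 1 extra visit and 7.1 with 3. A low count now marks early exit, and the CATCH-IT interviews raise the count at any given exit time.
- All contact counted in HEALTH EDUCATION but only the 3 interviews counted in CATCH-IT: HR 1.03 with 1 triggered visit per episode and 1.23 with 2.
- Contact counted to month 2, in youths then episode-free, with later episodes as outcome and 2 extra CATCH-IT visits: HR 1.04, rejection 4.8%. This shows that the episode-to-visit path is removed. It does not cover worsening mood before month 2 that raises both contact and later risk.

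**The case against.** The strongest reply is that the model simulated here is not a stated analysis. The sentence stands in a rationale section, offers evaluation as an alternative to control, and refers to the mediation analysis, whose own paragraph does not name physician encounters. The randomised attention-control arm is the first answer to the attention question, and the counting window could be left to an SAP. This limits the reach of the point. It does not remove it, because the protocol does state the intention to control for contact recorded during follow-up, and choosing a window does not by itself make that sound.

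Four stronger readings are tempting, and the documents do not support them:
- **That the Aim 1 test is biased.** The Cox comparison is not adjusted for contact.
- **That the adjustment always favours CATCH-IT.** This needs counts that run past the episode, extra CATCH-IT visits and triggered visits together. The only documentation rule stated concerns physician contact in HEALTH EDUCATION, and unequal recording points the other way.
- **That an episode generates more of the tracked calls.** Assessments and telephone monitoring are described as the same in both arms (item J; Benefits of study), and no text adds assessment calls after an episode.
- **That false benefit is near certain.** With 3 extra visits, the adjusted HR falls to 0.68, 0.52 and 0.40 for 0.5, 1 and 2 triggered visits (false benefit 42%, 90% and 99.7%). That requires the interviews to be wholly additional to routine visits, which no passage says. The 6.5 and 5.0 hours pool assessment, physician and Internet time, so they do not show extra visits either.

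It is also fair that notifying and re-contacting a physician is not a visit by the adolescent. Usual care and referral are the more direct route to extra visits, and the protocol gives no number for them.

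**Conclusion.** The point holds as a conditional one. The protocol proposes to control for a variable measured after randomisation that its own procedures can tie to both arm and outcome, so a contact-adjusted intervention effect cannot be read as the effect net of attention.

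For a difference of 0.5 to 1 visits and 0.5 to 2 triggered visits per episode, whole-follow-up counting gives an adjusted hazard ratio of about 0.94 to 0.73 under no effect, and false benefit in roughly 6% to 48% of trials. Both visit inputs are assumed. If either is zero, this bias disappears; if counting stops at the episode, it becomes apparent harm. The same null data could therefore support opposite conclusions under rules that the protocol leaves open. The harm is confined to the secondary claim about program versus attention.

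**What to change.** In the Rationale section, delete the words *control for* and state that no estimate of the intervention effect is conditioned on contact recorded during follow-up. Report site use, calls and physician encounters by arm descriptively.

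If attention is explored as a mediator, use only contact before the episode, recorded the same way in both arms. One workable form is contact to month 2 in youths who are then episode-free, with later episodes as the outcome. Label it exploratory, since early contact may still share causes with later episodes.

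The cost is one sentence in the Rationale and matching analysis wording. Recording physician contact alike in CATCH-IT may add some data collection. No clinical procedure changes. The trial gives up a contact-adjusted attention claim that it cannot support.

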**g. Safety Monitoring and Assessment (if relevant, include provisions for managing adverse reactions)**  
**Data management (when relevant, address measures of privacy protection, coding, storage of information)**

**DSMB plan:** A DSMB will convene every 6 months to review data. A report will be created by the analytic team led by [name]. Stopping rules will include: 1) clear advantage in primary outcome in any arm; and 2) evidence of adverse events significantly above that expected in this risk population in either arm.

#### **Risks of study and efforts to minimize risks:**

*General efforts to address/minimize risks:* A Data and Safety Monitoring Board (DSMB) will monitor our sites and serve as a reporting body to the NIH as well as the respective IRBs. Data will be reviewed after each fifteen persons complete the study. The primary role of the DSMB will be to monitor the safety of participants in both the Internet-based preventive intervention and HEALTH EDUCATION comparison group, report any and all adverse effects in a timely and consistent fashion, and check the validity and integrity of the data. The DSMB will be composed of four members, none directly involved in the project or employed by the participating institutions, and will include one psychiatrist (with experience working with adolescents), one psychologist, one pediatrician and one internist.

The DSMB will meet first to approve the protocol and subsequently conduct annual reviews to determine whether patient safety has been adequately safeguarded and enrollment goals have been met. The DSMB will be kept apprised of any adverse events when they occur and will serve as the final arbiters of whether individual patients should be removed from the protocol. Although the therapists, in consultation with the clinically responsible PI and/or co-Investigator, are empowered to take whatever immediate action is necessary to safeguard the welfare of individual patients, the DSMB also will be called upon to render judgments in the advent of any serious clinical problems (e.g., serious suicidal intent or clinical deterioration).

In addition, to protect the privacy of our participants, we will apply for a Certificate of Confidentiality from the Department of Health and Human Services (DHHS) for this research study. Participants and their families will thus be protected from disclosure of confidential information in federal, state, or local civil, criminal, administrative, legislative, or other proceedings. Disclosure will be necessary, however, upon request of DHHS for audit or program evaluation purposes. **The Confidentiality Certificate does not prevent subjects from voluntarily releasing information about themselves or their involvement in this research. The investigators may not use the Certificate of Confidentiality to withhold information when a participant gives written permission to provide research information to others.**

*Specific efforts to minimize risks.* The proposed study poses minimal risks. Those risks that might exist fall into four categories: (a) risks of the preventive intervention; (b) risks associated with research assessments, consisting of face-to-face questions about depression, family and personal functioning, and other mental and emotional problems; (c) risks associated with potential loss of confidentiality; and (d) risks of worsening mental or emotional state. We address each in turn below.

*A) Risks of the preventive intervention.* The Internet-based preventive program consists of 14 modules that teens complete independently. In previous studies we did not find adverse effects of the Internet-based prevention program. However, there is the slight possibility that some teens may find it slightly uncomfortable to think about the feelings and attitudes that are highlighted in the Internet-based program.

*Protection for risks of the preventive intervention:* Youth participating in the Internet-based prevention program will be told that, if they experience any discomfort as a result of their participation, they should discuss any feelings of discomfort with members of the research staff. Research staff will talk with participants about the nature of their discomfort and will encourage them to take breaks or discontinue modules that they find uncomfortable. We will conduct safety surveillance calls for those in the CATCH-IT 3 arm at 1 week and 1, 2, 6, 12, and 24 months. Should we be unable to reach a participant at two consecutive time points, we will utilize public records or locator services to attempt additional contact to ensure the safety of the family.

*B) Risks associated with research assessments:* As noted, research assessments consist of face-to-face questions about depression, family and personal functioning, and other mental and emotional problems. Youth will give voluntary responses to interview questions; they are told that they can decline to answer any questions that they want, if answering would cause them distress or concern. We or our colleagues have used all of these instruments in previous research with no known problems or distress on the part of the participants. All research assessments are audio-recorded, for the purpose of review by senior research staff who make quality assurance ratings of staff performance. These audio-recordings are another form of research data that is at slight risk for unintentional release to unauthorized persons.

*Protection for risks associated with research assessments:* Youth and parents will be told that they are free to not respond or to terminate involvement at any time, with no adverse consequences. If a youth or parent appears to be distressed during assessments, research staff will halt the interview and offer to take a break. The interview will only recommence when and if the participant reports feeling capable of doing so. The interviews during the course of the study involve no specific risk or discomfort beyond those of a standard clinical interview. Interviewers will be trained to be sensitive to these issues.

C) *Risks associated with potential loss of confidentiality.* As noted above, there is a slight risk that research records (questionnaires, chart notes) might be obtained by persons not authorized to do so. There is a slight risk that research data files might be compromised and obtained or viewed by unauthorized persons. Finally, the strategy used to identify potential participants, screening questionnaires administered in the waiting room, carries the potential risk of loss of privacy. The risk of this method is that participants would experience a loss of confidentiality if others in the waiting room were to see their responses on the questionnaire form.

*Protection for risks associated with potential loss of confidentiality.* Data for all participants will be kept strictly confidential, except as mandated by law. All research files are kept in locked file cabinets or a locked file room. Participants will be assigned a numerical code for identification in the files. Names and other identifiers will be kept in separate locked files. Statistical analyses will be performed on aggregate-level data; participants are never individually named. All audio-recorded assessments and motivational interviews will be kept in locked file cabinets and will never be played for anyone who is not a member of the research team.

D) *Risks of worsening mental or emotional state and or self-harm thoughts/events.* Some youth enrolled in the Internet-based prevention program, and in the control group, will likely develop depression, suicidal behavior, and/or other mental and emotional problems during the study period. The development of suicidal ideation during the study remains as the most serious risk. However, these are risks inherent in the population and would occur whether or not they were enrolled in the study. We do not believe that the risk of these depressive, suicidal, or other adverse outcomes are increased as a function of being enrolled in this study. Should mood worsen or thoughts of self-harm develop (i.e. teen develop MDD, MDE, or suicidal thoughts), the teen's physician and parents will be notified. Physicians will be recontacted 1 week after disclosure to inquire as to whether the teen has begun treatment or a treatment plan is in place. Should no plan/treatment yet be established, PI or Project Manager will discuss with doctor the best course of action for the teen to ensure their safety and connection to mental health services.

*Protection against risk of worsening mental or emotional state:* Throughout the study, both intervention and control participants will be monitored regularly for evidence of symptom change. We will ask participants at each evaluation point whether they have or are experiencing negative emotions as a result of the intervention. Additionally, any individual with high sub-threshold depression (four symptoms as well as functional impairment) at evaluation points will be offered referral to a mental health specialist. If, during any assessment or intervention contact, research staff determine that either a youth or parent has developed a serious mental health problem (including but not limited to worsening depression, suicidal behavior, etc.), we will provide referral information and the telephone numbers to appropriate services ("usual care" for these conditions). If the detected problem is imminent and of crisis status, we will take appropriate immediate action, including escorting and/or providing medical transportation for these individuals to an emergency room. A Data Safety and Monitoring Board will be set up to monitor any adverse events that might occur during the course of the study (see description below).

*Protection against risk of self-harm thoughts/acts:* We have developed detailed procedures for detecting, assessing and triaging youth with psychiatric emergencies. The most frequent, although rare, of these crises involves suicidal behavior (not surprising given the depression risk of these youth) but includes acute substance abuse, psychotic symptoms, and so on. To address the risk of suicide we will conduct safety surveillance calls for those in the CATCH-IT 3 arm at 1, 4, 8 week and 6, 12, 18 and 24 months. We will also conduct post-study monitoring by telephone at 12 and 24 weeks. Monitoring during the intervention will include follow-up phone calls from the study coordinator four weeks after enrollment to assess for suicidal ideation and/or worsening depression symptoms. We will reassess for suicide risk and Major Depression at the exit interview. Because of our extensive and repeated assessment procedures, we believe we will be aware of suicidal thoughts/intentions, should they exist, and we are well prepared to manage these issues. In fact, given the high incidence of suicidal thinking among adolescents, it is likely that participants in this study with suicidal thoughts will be *more* likely to receive appropriate referrals, treatment and follow-up than will adolescents who

are not part of this research project. All participants who develop suicidal ideation will be referred for further evaluation by a child psychiatrist. The principal investigator will remain available on 24-hour call for adolescent participants or their parents should a need or concern arise. Briefly, any one of several “trigger events” (such as a positive response to a suicide assessment item, or suicidal behavior in sessions) requires staff to collect more detailed information about the possible crisis event. In the case of suicide, several specialized scales may be administered (the Suicide Intent Scale and the Suicide Ideation Scale), not for data but to aid in clinical decision-making. When sufficient information regarding the possible crisis is obtained, staff will use decision rules to decide whether the risk is (a) high and imminent or (b) high but not imminent. For the imminent risk situations they immediately link the subject to emergency mental health resources. This may include the use of security personnel to escort the youth to the appropriate facility, or enlisting parents to escort the youth. For events that are risky but not imminent, staff will contact the clinically-responsible investigators (the site PIs and co-investigators) for consultation. Follow-up for less-imminent risk events typically will include informing the parent(s) and other involved clinicians, and providing referrals. Because “usual care” is permitted in both study conditions, all youth will be referred to the usual crisis resources in their community. The intent of the research emergency protocol is not to offer more research intervention services, but to detect, assess, and triage/refer the youth to the most appropriate existing, non-research crisis resource available to them.

**Self-harm prevention protocol:** This protocol specifies assessment and management of risk during the study and includes structured assessment, risk stratification and actions to be taken.

**PATH Abuse Protocol:** A safety protocol has been developed to address any thoughts or actions of harm to others that are disclosed during any point of contact with the participant. Action will be taken to ensure immediate safety needs are met, followed by disclosure to parent and/or healthcare provider as necessary. Research staff will also provide assistance locating mental health services and notify any appropriate authorities in these circumstances.

**Unique risks of a multi-site study:** In a multi-site study of this type, some of the assessments and motivational interviews will be sent to the coordinating center for quality assurance (reliability and fidelity) ratings. These files, audio-recordings and other data will be identified only by the non-meaningful research ID (001, 002, etc.) and will not have any identifying information on it. Only authorized research staff at the other site will review these research audio-recordings, files or data, and then only for the purposes of quality assurance and/or research training. Data sent to remote sites such as the coordinating center also will be kept locked and secure at those sites, using the same procedures identified here in this section. All computerized data will be kept on the secured computers or networks at each site. These data will be accessible only to research staff, using confidential usernames and passwords.

